**Figure 1 F1:**
[figure not shown]
CONSORT flowchart of patient enrollment.

A safety, futility, and superiority interim analysis will be performed by the DSMB after 175, 350, 500 (safety and futility) and 1,000 (safety and superiority) patients are included. Differences in serious adverse events between intervention and placebo are used for safety analyses and the primary endpoint 28-day survival is used to determine futility or superiority of intervention or placebo.

After the inclusion of 1,000 patients, superiority will be tested. A proven superiority (*P < 0.003, two-sided)* of any dose of haloperidol over placebo or a proven superiority (*P < 0.003, two-sided)* of placebo over haloperidol determined during the interim analysis will result in an alpha of 0.049 (two-sided) for the final analysis. This alpha distribution was calculated by an independent statistician according to the method of Lan-DeMets cumulative alpha spending function of O’Brien-Fleming alpha spending [36].

Data will be analyzed according to the intention-to-treat principle. For the descriptive statistics, continuous variables will be given as mean with standard deviation or median and inter quartile ranges, depending on their distribution. Normally distributed variables will be tested using Student’s *t*-test for comparison and Mann-Whitney U-tests for non-normally distributed variables. Categorical (and binary) variables will be presented as numbers and percentages and will be analyzed using the χ^2^ test. Survival analyses with Kaplan-Meier curves will be used as graphical representation. Cox proportional hazard regression analyses will be used to estimate the hazard ratio for survival with the use of haloperidol versus placebo. Furthermore, we will perform adjusted analyses for relevant covariates (including delirium, APACHE-II score, age, sex, sepsis, and other differences between the three study groups irrespective of the possible imbalance between the three groups). For this covariate analysis, univariate logistic regression analysis will be performed first in order to test the strength of the relationship. Subsequently, variables significantly associated with the dependent variable will be included in the covariate analyses.

Furthermore, subgroup analysis will be performed by direct comparisons of *a priori* specified subgroups, i.e., predicted risk group, admission type group, and APACHE-II group, in order to determine effectiveness of prophylactic haloperidol treatment in these subgroups on 28-day survival.

All statistical tests are two-sided and statistical significance is defined as a *P* value < 0.05. All data will be analyzed using SPSS version 20.01 (SPSS, Chicago, IL, USA).

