### Sample size calculation and statistics

Sample size calculation is based on the difference in survival from our previous prophylactic haloperidol study [19]. In this study, the median survival time in the control group was 18 days. If the true hazard ratio of control patients relative to intervention patients is 0.85, taking into account an accrual time of 90 days with 28 days of follow-up, we will need to study 647 patients per intervention group and 647 control patients to be able to reject the null hypothesis that the experimental and control survival curves are equal with probability (power) 0.80. The Type I error probability associated with this null hypothesis test is 0.05. Taking into account a dropout percentage of 10%, we will include 715 patients per group (Figure 1). A fixed sequence procedure will be followed. First, the highest dosage of prophylactic haloperidol will be compared with placebo using alpha 0.05 (two-sided). Only if H_0_ is rejected, subsequently the lower dosage of prophylactic haloperidol will be compared with placebo. Cox regression analysis will be used to test differences on 28-day survival in the intervention group compared with the placebo group.

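### The final alpha of 0.049 is tied to interim success while 0.05 is stated elsewhere, and the interim sits outside the fixed sequence: a contradictory primary decision rule, with a small excess of error

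*Protocol article*

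**What the plan says.** All statements are in the protocol article, under Sample size calculation and statistics.

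- **Sample size paragraph.** The design level is 0.05: "The Type I error probability associated with this null hypothesis test is 0.05". For the primary comparison: "First, the highest dosage of prophylactic haloperidol will be compared with placebo using alpha 0.05 (two-sided"). The lower dose comes second: "Only if H_0_ is rejected, subsequently the lower dosage of prophylactic haloperidol will be compared with placebo".
- **Interim paragraph, after Figure 1.** At 1,000 included patients superiority is tested at P < 0.003, two-sided. The claim may be "of any dose of haloperidol over placebo or a proven superiority" of placebo over haloperidol. Either finding, "determined during the interim analysis will result in an alpha of 0.049 (two-sided) for the final analysis". The pair 0.003 and 0.049 is attributed to a Lan-DeMets spending function of O'Brien-Fleming type.
- **Closing paragraph.** "All statistical tests are two-sided and statistical significance is defined as a" P value below 0.05, with no exception for the primary endpoint.

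The section does not say which level applies at the end if the interim boundary is not crossed, whether the fixed sequence governs the interim, or what follows from a crossing.

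**The concern.** Alpha is spent by taking an interim look, whatever it shows. The reduced level should therefore apply to every trial that goes on to a final test. The text instead ties 0.049 to a crossed boundary. It leaves the ordinary case, boundary not crossed and trial continued, with no stated level except the 0.05 given elsewhere in the section.

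Separately, the interim wording allows 1 mg to be proven superior without 2 mg having succeeded, which the fixed sequence rules out. Correcting the 0.049 sentence would not remove this second conflict.

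What is at stake is the success criterion of the primary endpoint. Two analysts could apply the document to the same result and disagree.

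**Working it through.** **Inputs from the protocol article**
- Superiority look at 1,000 patients; total 2,145 (715 per group).
- Interim level 0.003 per comparison, two-sided; final level 0.049 or 0.05, two-sided.
- 2 mg tested first, 1 mg second.

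**Assumptions**
- Information is proportional to enrolment: t = 1,000/2,145 = 0.466.
- The two dose comparisons have correlation 0.5, from the shared placebo group and equal allocation.
- The looks at 175, 350 and 500 patients, labelled safety and futility, spend no efficacy alpha.

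**1. The plan's own pair.** The spending function is α(t) = 2[1 − Φ(1.96/√t)]. The final level comes from the bivariate normal with correlation √t between the interim and final statistics.
- α(t) = 0.003 at t = 0.436, and the matching final level is 0.0488, which rounds to 0.049.
- At t = 0.466 the function gives 0.0041 and 0.0483. With 0.003 held fixed at that t, the final level is 0.0489, again 0.049.

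So 0.003 and 0.049 are a sound split for one comparison, provided 0.049 applies whenever the trial continues.

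**2. One comparison, 2 mg versus placebo.** Error = P(|Z₁| > z at 0.003, or |Z₂| > z at the final level), with corr(Z₁, Z₂) = √0.466 = 0.683.
- 0.003 then 0.05: 5.11%.
- 0.003 then 0.049: 5.01%.

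**3. Both doses, no true effect of either.** The statistics are interim 2 mg, interim 1 mg and final 2 mg, taken as trivariate normal and confirmed by simulation. A 1 mg crossing at the interim counts as a claim.

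| Interim rule | Final level | Two-sided familywise error |
|---|---|---|
| Either dose at 0.003 | 0.05 | 5.35% |
| Either dose at 0.003 | 0.049 | 5.25% |
| 2 mg first, 1 mg only if 2 mg crosses | 0.049 | 5.01% |
| 2 mg first for benefit, placebo-better boundary kept for each dose | 0.049 | 5.1% |
| 0.003 split as 0.0015 per dose | 0.049 | 5.06% |

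The chance of at least one false crossing at the interim is 0.58% under the either-dose rule, against 0.30% for one comparison. For t from 0.436 to 0.50, the first row runs from 5.36% to 5.33%, so the timing assumption matters little.

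**4. Where the excess comes from.** Using 0.05 instead of 0.049 adds 5.11 − 5.01 = 0.10 points. The either-dose rule adds 5.35 − 5.11 = 0.24 points.

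**The case against.** The best defence is that the 0.049 sentence is a slip over a sound design. The article presents 0.003 and 0.049 as an alpha distribution from a spending function, and such a split makes sense only if 0.049 applies when the trial continues. The 0.05 for the high-dose test can then be read as the overall level being distributed, and the closing 0.05 as a general convention that the specific rule overrides. The fixed sequence is not expressly limited to the final analysis. The action after a crossing may sit in a monitoring charter or in the full protocol, neither of which is shown.

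Much of this stands. A reader might infer that the plan reverts to 0.05 when the boundary is not crossed. The document does not state that; it is an inference from the other paragraphs. A reader might also infer that error control breaks down. That is too strong, for three reasons:
- The 5.35% treats a 1 mg crossing at the interim as a confirmatory claim, which the text does not say.
- It is a two-sided count that includes false findings of harm. Counting false benefit claims only, with 0.05 at the final, the figure is 2.68% against 2.56% when only 2 mg is tested at the interim.
- On the charitable reading of the final level, the 2 mg comparison is held at 5.01%.

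The contradiction itself remains. The article chose to print all of these levels, and nothing in it says which prevails. The either-dose wording cannot be squared with the fixed sequence without a further statement.

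**Conclusion.** The concern holds as a contradiction in the primary decision rule with a small numerical consequence. The article gives 0.049 only as the result of interim success, states 0.05 elsewhere for the same test, and leaves a final P between 0.049 and 0.05 open to either reading. It also lets either dose succeed at the interim, in conflict with the fixed sequence.

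On the literal reading (0.05 at the end if the interim is not crossed, and a low-dose crossing counted as a claim), the excess over 5% is about 0.1 points for 2 mg and at most about 0.35 points familywise. With 0.049 at the end, the familywise excess is about 0.25 points. These figures rest on an information fraction of 0.466, correlation 0.5, and no efficacy alpha spent at the first three looks. The reason to act is the ambiguous threshold more than the size of the inflation.

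**What to change.** 1. State that 0.049 (two-sided) applies to both steps of the final fixed sequence whenever the trial continues past the 1,000-patient look.
2. In the sample size paragraph, describe 0.05 as the overall level. In the closing paragraph, exempt the primary endpoint from the general 0.05.
3. Apply the same sequence to efficacy claims at the interim: 2 mg at 0.003 first, 1 mg only if 2 mg crosses. With the sequence applied in both directions, error is about 5.0%. The alternative is to split the 0.003 between the doses. With 0.0015 each and 0.049 at the end this gives 5.06%, so the final level should then be recalculated (about 0.048).
4. If a placebo-better boundary is kept for each dose, present it as a safety boundary outside the efficacy alpha. Counted two-sided with the rest, it brings the total to about 5.1%.
5. Replace the clause that makes 0.049 the result of a crossing with a statement of what a crossing leads to, or refer to the document that governs it.

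The cost is a few sentences and no change in sample size. Power hardly moves: with a true high-dose effect giving an expected final Z of 2.8, the simulated chance of some rejection is 80.2% with 0.05 and 79.9% with 0.049 (either-dose rule at the interim in both). The low dose loses its unsequenced chance at the interim. The article's trial status says preparations were nearing completion, so the text can be settled before any outcome data are seen.

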### Data collection

All data will be collected electronically in an electronic CRF (E-CRF). The E-CRF is a secured website where the participating hospitals must login using a unique password. Participating hospitals will only have access to their own data.

Demographic variables will be collected from all patients, including age, gender, PRE-DELIRIC score, APACHE-II score, and diagnosis group. Furthermore, outcome related variables will be collected (Table 2) as well as variables that may influence the delirium outcome, i.e., dexmedetomidine [32] and early mobilization [33]. Concerning the study medication, we will collect data on the amount of study drug administered as well as open-label haloperidol and other anti-delirium drugs administered in case delirium occurs.

**Table 2 T2:** Primary, secondary endpoints and posthoc analyses

**Primary endpoint**	**Secondary endpoints**	**Post-hoc analyses**
28-day mortality	90-day mortality Delirium incidence	Effectiveness in groups of predicted risk up to 50%, 50–70%, 70–90%, above 90% will be evaluated
	Number of delirium and coma free-days in 28 days	Effectiveness in diagnosis groups: medical, surgical and trauma patients
	Duration of mechanical ventilation	Effectiveness per APACHE-II score: <20, 20–25, >25
	Incidence of unintended tube or catheter removal	Effectiveness in groups with 1, 2, or more positive CAM-ICU scores
	Incidence of ICU re-admission	
	Quality of life measured at time of ICU admission, after 1 and 6 months using SF-12	
	Incidence and severity of side effects of prophylactic haloperidol (all patients)	

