## Discussion and trial status

This is the first large-scale multicenter randomized-controlled prevention study with haloperidol in ICU patients with an increased risk to develop delirium. The study design and protocol was finalized in 2012 and the protocol passed the medical ethical committee on February 2013. Prior to the start of the study, all centers will be visited to inform all involved researchers and a second meeting will take place as an initiation visit. Furthermore, a meeting with the DSMB and the monitor will be scheduled prior to the conduction of the study.

Results of our study will be of importance for critically ill patients and permits us to draw conclusions on the effectiveness of haloperidol prophylaxis in reducing 28-day mortality, preventing delirium, and improving delirium-related outcome. Furthermore, it will provide information regarding the delirium-risk category in which the PRE-DELIRIC model prophylaxis is most effective. Positive effects of haloperidol prophylaxis on delirium outcome will result in the alteration of daily practice for critically ill patients and would therefore have major implications. However, if there is no effect of haloperidol prophylaxis, other possibilities of delirium prevention, such as nursing interventions, need to be studied. In addition, the effectiveness of nursing interventions focusing on delirium prevention can be studied in conjunction with haloperidol prophylaxis.

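### The only tests stated that fit delirium incidence and delirium-and-coma-free days are unadjusted: valid, but prognostic baseline variables go unused and efficiency is lost

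*Protocol article*

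**What the plan says.** All places are in the protocol article.

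- **Sample size calculation and statistics** (text after Figure 1) assigns tests by type of variable. For binary data: "Categorical (and binary) variables will be presented as numbers and percentages and will be analyzed using the" chi-square test. For continuous data, Student's t-test if normally distributed, otherwise "Mann-Whitney U-tests for non-normally distributed variables". No endpoint is named.
- The same paragraph ties Cox regression to survival and then continues: "Furthermore, we will perform adjusted analyses for relevant covariates (including delirium, APACHE-II score, age, sex, sepsis" and other between-group differences. The dependent variable is not named. Covariates enter after a univariate logistic screen for significance.
- **Secondary objectives** 2 and 3 are delirium incidence and delirium-and-coma-free days in 28 days.
- **Data collection**: "Demographic variables will be collected from all patients, including age, gender, PRE-DELIRIC score, APACHE-II score, and diagnosis group".
- **Discussion and trial status**: "Positive effects of haloperidol prophylaxis on delirium outcome will result in the alteration of daily practice for critically ill patients".

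**The concern.** The authors cite their own validated model for predicting delirium, so by their account part of the variation in delirium between patients can be explained by what is known about them. The plan uses patient factors of this kind in an adjusted analysis that reads as survival, while the only tests that fit the two delirium outcomes ignore them. An unadjusted test leaves explainable variation in the error term. The confidence interval is then wider than it need be, and the chance of detecting a real preventive effect is lower. This matters more than usual for secondary outcomes, because the article says that delirium results will alter daily practice.

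**Working it through.** **1. Which stated analysis fits which outcome.** Delirium incidence is binary, so the chi-square line covers it. Delirium-and-coma-free days is a count of days, so the t-test or Mann-Whitney line covers it; the article does not say which. The adjusted analysis follows the Cox sentence and lists delirium as a covariate. It cannot sensibly be a model for delirium incidence, and it would be circular for delirium-free days.

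**2. The plan's own figure.** The article states no power for either delirium outcome. Its 647 per group is for survival and reproduces:
- Events = 4(1.96 + 0.842)² / (ln 0.85)² = 1,189.
- With exponential survival, an 18-day control median, 90 days of accrual, 28 days of further follow-up and the hazard ratio taken in the direction worded, the event probabilities are 0.905 and 0.932, mean 0.9185.
- 1,189 / (2 × 0.9185) = 647.

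It is used below only as the number per arm.

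**3. Inputs for incidence.**
- n = 647 per arm; two-sided alpha 0.05 (Sample size calculation and statistics).
- Control incidence 35%: an assumption, taken from the median predicted risk in Background.
- Treated incidence 28%: an assumption with no source in the documents. Also 30.3%, from 35% × 65/75, the ratio in the earlier high-risk study.
- 75% versus 65%: the incidences in that earlier study, which selected patients with predicted risk above 50%.
- Predictive strength of the covariates: not in the documents. Assumed AUC 0.65 to 0.80.

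**4. Unadjusted power.** SE = √[(p₁(1−p₁) + p₂(1−p₂)) / n]; power = Φ(|p₁−p₂|/SE − 1.96).
- 35% v 28%: SE = √[(0.2275 + 0.2016)/647] = 0.02575; Φ(2.718 − 1.96) = 0.776.
- 35% v 30.3%: SE = 0.02604; Φ(1.792 − 1.96) = 0.43.
- 75% v 65%: SE = √[(0.1875 + 0.2275)/647] = 0.02533; Φ(3.949 − 1.96) = 0.977.

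**5. Adjusted power.** If covariates explain a share R² of the outcome variance, the SE is multiplied by √(1 − R²). At 35% incidence, a logistic model with one normal risk score gives R² = 0.051 at AUC 0.636, 0.140 at 0.722, 0.212 at 0.772 and 0.303 at 0.827. Interpolating, AUC 0.65 corresponds to R² of about 0.066 and AUC 0.80 to about 0.258.

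| Incidence | Unadjusted | AUC 0.65 | AUC 0.80 |
|---|---|---|---|
| 35% v 28% | 0.78 | Φ(0.07/0.02490 − 1.96) = 0.80 | Φ(0.07/0.02218 − 1.96) = 0.88 |
| 35% v 30.3% | 0.43 | 0.46 | 0.55 |

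The variance ratio 1/(1 − R²) runs from 1.07 to 1.35, equivalent to about 7% to 35% more patients. At 75% v 65%, power goes from 0.977 to 0.982 at R² = 0.05 and to 0.999 at R² = 0.40, a gain of about two points at most.

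**6. Simulation check.** Simulated trials with 647 per arm, comparing chi-square with adjusted logistic regression, gave about 0.77 unadjusted for 35% v 28%. Adjusted power was 0.79 to 0.80 at AUC 0.65 and 0.87 to 0.89 at AUC 0.80. For 35% v 30.3% it rose from 0.43–0.44 to 0.45–0.47 and 0.53–0.57 respectively. Under no effect, both methods rejected in about 5% of trials (0.046 to 0.060).

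**7. Days outcome.** No gain was computed for delirium-and-coma-free days.

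**The case against.** The strongest reply is that nothing here is wrong. Randomisation makes the unadjusted tests valid, and their intervals already allow for chance imbalance. That stands: the point is one of efficiency only. A reader might infer bias or an inflated type I error, and neither the text nor the calculations support that.

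Second, the test list opens with "For the descriptive statistics, continuous variables will be given as mean with standard deviation or median and inter quartile ranges" and is generic. A reader might infer that the article assigns Mann-Whitney to delirium-and-coma-free days; it does not. An analysis plan not shown may assign the tests. Even so, the article states these as tests to be used, and no other stated test fits the two outcomes.

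Third, the adjusted analysis names no outcome, and its logistic screen would suit a binary one. A reader might infer that adjustment of the delirium outcomes has been ruled out. The text leaves it unclear, although delirium in the covariate list makes survival the natural reading.

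Fourth, the predictability cited in Background is that of PRE-DELIRIC, which Background says is possible only 24 hours after admission, whereas Ethics has the study drug starting immediately. Its strength cannot be borrowed for age, sex and admission type alone, and the AUC range is therefore an assumption. The timing of APACHE-II is not stated, and Data collection does not name sepsis. It would be too much to say that every useful covariate is already available as a pre-dose value.

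**Conclusion.** The point holds as a loss of efficiency on two secondary outcomes to which the article gives practice-changing weight. For incidence, at an assumed 35% versus 28% and 647 per arm, adjustment would raise power from about 0.77 to about 0.80 to 0.89, if the covariates reach an AUC of 0.65 to 0.80. At the lower end the gain is two or three points. At 35% versus 30.3% it helps but leaves power near one half, and at 75% versus 65% it is negligible because power is already 0.98. The actual gain cannot be read from the documents, and for delirium-and-coma-free days its size is unknown. The change is worth making because it requires only wording and the unadjusted result is still reported.

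**What to change.** In Sample size calculation and statistics:

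- Make the main test of delirium incidence a logistic model with treatment and a fixed list of covariates whose values are set before the first dose: age, sex and admission type. Add APACHE-II, PRE-DELIRIC and sepsis only if they are recorded from pre-dose values.
- Use no significance screening for these covariates, and do not include delirium as a covariate.
- Report the covariate-standardised risk difference with its 95% confidence interval, so that the estimate stays marginal.
- Analyse delirium-and-coma-free days with a proportional-odds model on the same covariates.
- Keep the chi-square and the t-test or Mann-Whitney results as supportive.
- Name the outcome of the existing adjusted analysis.

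Cost: a wording change, to be fixed before unblinding. No extra patients are needed; age, sex and diagnosis group are already collected. The price is slightly more complex modelling and, for the days outcome, reliance on the proportional-odds assumption.
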